### 1.1. Research Question

This feasibility study aims to determine whether a brief, stand-alone, synchronous online mentalization-based video-feedback intervention (VFI-RF) can be successfully delivered and evaluated among mothers experiencing postnatal risk conditions.

Specifically, the study will address the following research questions:Can eligible mothers be successfully identified, recruited, and retained across the study period?Are the assessment procedures, including questionnaire completion and follow-up assessments, feasible and acceptable to participants?Are the privacy, video-sharing, and data management procedures acceptable and implementable in a fully online format?Do participant-reported satisfaction and qualitative feedback support the acceptability of the VFI-RF intervention and study procedures?

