### 1.2. Primary Outcomes

The primary objective of this study will be to generate preliminary evidence on the feasibility and acceptability of delivering and evaluating the VFI-RF intervention for mothers at risk during the postnatal period. In line with the aims of a feasibility study, the primary outcomes focus on feasibility and acceptability indicators rather than intervention effectiveness.

Feasibility will be assessed through enrolment indicators, including the number of mothers referred, the proportion deemed eligible, and the proportion of eligible mothers who provide informed consent. Additional feasibility indicators include intervention uptake, measured as the proportion of VFI-RF sessions attended, retention at baseline and follow-up, reasons for ineligibility or withdrawal, assessment completion, and the extent of missing data on key measures.

Feasibility indicators will be calculated using predefined denominators. Specifically, the number of mothers referred will represent all mothers referred to the study by participating services or who self-refer following study advertisements. Eligibility rate will be calculated as the proportion of referred mothers meeting inclusion criteria. Consent rate will be calculated as the proportion of eligible mothers who provide informed consent. Intervention uptake will be calculated as the proportion of scheduled VFI-RF sessions attended. Retention rates will be calculated as the proportion of consented participants completing each assessment time point (T0, T1, and T2). Assessment completion rates will be calculated as the proportion of participants who complete the planned questionnaires at each assessment wave. All feasibility indicators will be reported for the overall sample and separately for each risk group (i.e., Risk Group 1: anxiety/depression; Risk Group 2: preterm birth).

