#### 2.1.6. Procedure

Mothers who meet the inclusion criteria and voluntarily consent to participate will be sent a link to complete the baseline survey. Eligible mothers will complete the baseline assessment (T0) when their infants are approximately 3 months of age. Baseline measures will include self-report questionnaires assessing sociodemographic information, maternal reflective functioning, psychological distress, parenting stress, perceived social support, and attachment style. Mothers will then be invited to attend a virtual appointment (within the same week) to review and discuss baseline findings. Prior to the online meeting, a clinician with psychodynamic training will review the mother’s responses. During the first session, the clinician will conduct a clinical interview to clarify any ambiguous findings and to establish an initial therapeutic engagement. The intervention procedures will be agreed in detail with each participant. Specifically, mothers will be instructed on how to use the platform, a schedule of sessions will be established, and clear guidance will be provided on how to record the video, where and how to upload/send it, and the sequence of everyday caregiving routines to be filmed. During the video-feedback sessions, selected moments of mother–infant interaction (e.g., feeding, diaper changing) previously recorded by mothers and submitted to the researcher will be reviewed and discussed jointly.

The privacy and confidentiality of all video recordings will be strictly protected. Mothers will receive an individualized secure link to a dedicated cloud-based storage system accessible only to the researcher. Uploaded videos will be stored using a pseudonymized alphanumeric participant code. The code will be generated using the first two letters of the participant’s first name, the first two letters of the participant’s surname, and the last two digits of the participant’s year of birth. No full names or other directly identifying information will be included in the video file names.

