Following completion of T0, mothers will participate in a structured mentalization-based video-feedback program delivered synchronously online over a five-month period, comprising ten fortnightly sessions. During the intervention, mothers will be asked to record brief videos (approximately 5 min) of everyday caregiving interactions with their infant following standardized instructions. Recordings will be shared securely with the clinician and reviewed during online sessions, in which selected interaction sequences will be collaboratively explored to promote maternal reflective functioning and sensitivity (see Section 2.1.7).

Post-intervention assessment (T1) will be completed when infants are approximately 8 months of age, using the same procedures as at baseline. A follow-up assessment (T2) will be conducted when infants are approximately 12 months old to examine the maintenance of effects over time. At both time points, participant feedback will also be collected to explore mothers’ experiences of and satisfaction with the VFI-RF (see Figure 1).

All assessments and intervention sessions will be conducted remotely via secure digital platforms (e.g., Qualtrics, Zoom, Teams), in accordance with data protection and ethical requirements. Clinicians and research staff involved in data collection and observational coding will follow standardized protocols to ensure consistency and reliability across time points and study sites.

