##### Dosage and Administration

The intervention will consist of eight VFI-RF sessions (approximately 50 min per session) delivered over 5 months. A two-week interval between sessions (Phase 2) was selected to allow mothers sufficient time to record brief everyday interactions, upload them securely to the clinician, and enable the clinician to review the material and discuss it within the research team prior to the session. All sessions will be delivered by the same trained psychologist, who works within a psychodynamic framework and has received specific training in the use of video-feedback. Participation is entirely voluntary, and participants may withdraw at any time and/or decline to take part in any specific intervention component. Pending the outcome of the study, the treatment manual will be available upon request.

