### Strengths and Limitations

Although the fully online delivery of the intervention may represent an important advantage for mothers whose personal, geographical, clinical, or caregiving circumstances limit access to in-person perinatal services, some limitations should also be acknowledged. The online format has the potential to increase accessibility and reduce logistical barriers while preserving the core reflective component of video-feedback work; however, it may also exclude mothers without suitable electronic devices, a stable internet connection, sufficient digital literacy, or access to a private space for participation.

Most importantly, the single-arm feasibility design does not allow causal conclusions regarding intervention effectiveness. Any observed trajectories over time may reflect infant maturation, spontaneous improvement in maternal distress, regression to the mean, repeated assessment, or nonspecific therapeutic factors, rather than the specific effects of the VFI-RF. The relatively small feasibility sample will also limit conclusions about differential responses across risk profiles or potential mechanisms of change. Accordingly, analyses of clinical outcomes, risk profiles, and reflective functioning will be interpreted as exploratory and hypothesis-generating.

In addition, reliance on self-report measures for some outcomes may introduce reporting biases, particularly among mothers experiencing psychological distress [7]. Self-selection bias may also occur, as mothers experiencing greater difficulties, or conversely those who are more motivated and available to engage in reflective work, may be more likely to participate. Finally, the home environment may vary considerably across participants, potentially affecting the quality, comparability, and emotional context of recorded interactions. Privacy may also be more difficult to ensure during online sessions, particularly in crowded households or when a quiet and confidential space is unavailable. These issues will be specifically monitored through feasibility indicators and qualitative feedback and will inform refinements to privacy procedures, clinician support, and strategies to reduce participant burden in a future randomized controlled trial.

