**Figure 2 jcm-15-05271-f002:**
[figure not shown]
Structure and content of the VFI-RF.

**Table 1 jcm-15-05271-t001:** Progression criteria for feasibility and acceptability.

Domain	Area	Indicator	Green	Amber	Red
Feasibility	Enrolment	Mothers referred	≥80% of target	60–79%	<60%
		Eligible among referred	≥60%	40–59%	<40%
		Consented among eligible	≥70%	50–69%	<50%
	Intervention uptake	VFI-RF sessions attended	≥75%	50–74%	<50%
	Retention	Baseline participation	≥90%	75–89%	<75%
		Follow-up participation	≥80%	65–79%	<65%
		Ineligibility/withdrawal reasons across study phases	Infrequent/ non-systematic	Modifiable reasons	Recurrent major issues
	Assessment/data quality	Assessments completed	≥85%	70–84%	<70%
		Missing data on key measures	≤10%	11–20%	>20%
Acceptability	Assessment procedures	Number/frequency acceptable	≥75% positive	50–74%	<50%
		Duration/content/mode acceptable	≥75% positive	50–74%	<50%
	Mothers’ experience	VFI-RF experience	Predominantly positive	Mixed, with modifiable concerns	Predominantly negative or recurrent major concerns
		Satisfaction with VFI-RF/study procedures	≥75% satisfied	50–74%	<50%

**Table 2 jcm-15-05271-t002:** Schedule of participant assessment.

	Pre-Intervention		Post-Intervention	
	Screening	Baseline (T0)	Post-Treatment (T1)	Follow-Up (T2)
Demographics (e.g., age, education, employment and marital status), clinical history, and psychosocial risk variables	✔	✔		
Maternal reflective functioning (PRFQ)		✔	✔	✔
Maternal depression (EPDS)	✔	✔	✔	✔
Maternal anxiety (GAD-7)	✔	✔	✔	✔
Maternal Parenting stress- Short Form (PSI-SF)		✔	✔	✔
Maternal Perceived social support (MSPSS)		✔	✔	✔
Relationship Questionnaire (RQ)		✔		
Maternal postnatal attachment (MPAS)		✔	✔	✔
Child’s emotional and behavioral development (TAPQOL)		✔	✔	✔
Clinical Outcomes in Routine Evaluation- Outcome Measure (CORE-OM)		✔	✔	✔
Satisfaction questionnaire ad hoc			✔	✔

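### The uptake criterion divides by sessions scheduled, so mothers who never start largely drop out of it, and no indicator counts videos shared

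*Protocol article*

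**What the plan says.** Section 1.2 introduces the primary outcomes with "Feasibility indicators will be calculated using predefined denominators". For uptake the rule is "Intervention uptake will be calculated as the proportion of scheduled VFI-RF sessions attended". Retention, in the same paragraph, is instead a proportion of all consented participants.

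In Table 1 the row "VFI-RF sessions attended" is green at 75% or more, amber at 50–74% and red below 50%. It is the only row under intervention uptake.

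Section 2.1.6 invites each mother, after T0, to a first virtual appointment. It then describes what is agreed with her, including that "a schedule of sessions will be established".

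On the number of sessions, Section 2.1.6 has a programme "comprising ten fortnightly sessions", and Section 2.1.7 describes 8 + 2: Session 1 for assessment and engagement, Sessions 2–9 for video feedback, Session 10 for restitution. Dosage and Administration says "The intervention will consist of eight VFI-RF sessions".

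One research question in Section 1.1 asks: "Are the privacy, video-sharing, and data management procedures acceptable and implementable in a fully online format"? Strengths and Limitations, after discussing privacy and the home setting, says "These issues will be specifically monitored through feasibility indicators and qualitative feedback". Table 1 has no row for videos recorded, uploaded or reviewed, and none for privacy.

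**The concern.** Uptake should tell the investigators whether the intervention can be delivered to the mothers who agree to it. A denominator that exists only once a schedule has been agreed leaves out most of the evidence of the clearest failure, the mother who consents and never starts. For a mother who withdraws, the text supports two readings: her remaining sessions stay scheduled and count as missed, or they are no longer scheduled and disappear.

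Uptake is a primary progression criterion and feeds the choice in Section 1.3 between not feasible, feasible with changes, and feasible as designed. A wrong colour could carry an engagement problem unnoticed into the definitive trial.

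Videos raise a related problem. The video is the material of Sessions 2–9, and Dosage and Administration lets a mother decline any component. If she attends but shares no video, she still counts as full uptake.

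**Working it through.** The protocol gives no expected uptake, only the bands in Table 1, so there is no stated figure to reproduce. The check asks whether the choice of denominator changes the colour.

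**Inputs from the protocol article:** 48 mothers (Abstract; Section 2.1.4); ten sessions per mother (Section 2.1.6), with eight tried as well (Dosage and Administration); uptake green at 75% or more and red below 50%; follow-up participation green at 80% or more and red below 65% (Table 1).

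**Assumed:** the number of never-starters, *n*; the attendance of the mothers who start, *a*; all 48 complete T0; never-starters miss follow-up and everyone else completes it.

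**Formulas, ten sessions:**
- attended = (48 − *n*) × 10 × *a*
- uptake as written = attended / [(48 − *n*) × 10 + *n*], counting one missed first appointment per never-starter
- uptake on intended sessions = attended / (48 × 10)
- follow-up participation = (48 − *n*) / 48

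**Main illustration, *n* = 9, *a* = 0.90:**
- attended = 39 × 10 × 0.90 = 351
- as written: 351/(390 + 9) = 351/399 = 88.0%, green; with no first appointment counted, 351/390 = 90%, green
- on intended sessions: 351/480 = 73.1%, amber
- baseline participation 48/48 = 100%, green; follow-up 39/48 = 81.25%, green

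With eight sessions, attended is 39 × 8 × 0.90 = 280.8. Uptake as written is 280.8/(312 + 9) = 87.5%, and on intended sessions 280.8/384 = 73.1%. The colours are the same.

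**Sensitivity to the assumptions.** The first three rows use the smallest *n* that takes the intended-session measure below 75% at that attendance. The last is the smallest *n* that takes it below 50% at 90% attendance.

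| *a* | *n* | As written | Intended sessions | Follow-up |
|---|---|---|---|---|
| 0.80 | 4 | 352/444 = 79.3%, green | 352/480 = 73.3%, amber | 44/48 = 91.7%, green |
| 0.90 | 9 | 351/399 = 88.0%, green | 351/480 = 73.1%, amber | 39/48 = 81.25%, green |
| 1.00 | 13 | 350/363 = 96.4%, green | 350/480 = 72.9%, amber | 35/48 = 72.9%, amber |
| 0.90 | 22 | 234/282 = 83.0%, green | 234/480 = 48.75%, red | 26/48 = 54.2%, red |

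**Withdrawals, both readings.** Assume no never-starters, 12 withdrawals after session 3, and 90% attendance while active. Attended = 36 × 10 × 0.90 + 12 × 3 × 0.90 = 356.4. Counting only sessions up to withdrawal, 356.4/(360 + 36) = 90%, green. Keeping the whole schedule, 356.4/480 = 74.25%, below green. With eight sessions the second figure is (259.2 + 32.4)/384 = 75.9%, still green, so here the session count matters as well as the reading.

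**Videos.** A mother who attends 10 of 10 sessions and uploads nothing contributes 10/10 = 100% to uptake. No other row in Table 1 counts what she did not share.

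**The case against.** Four points can be made for the plan.

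1. **Withdrawals.** A reader might infer that withdrawn mothers always leave the denominator. The protocol does not say so. Section 2.1.6 can be read as setting a forward schedule at the start, in which case their later sessions remain and count as missed. This stands: the fault for withdrawals is an undefined term, not a stated exclusion. It does not help with never-starters, for whom at most the first appointment has been arranged.

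2. **Other rows would show the loss.** Retention uses all consented mothers, withdrawal reasons have their own row, and Section 2.2.1 has the criteria read together. This stands for large losses: with 22 never-starters who also miss follow-up, retention is red. It fails for moderate losses, as in the first two table rows, and when mothers stop sessions but keep completing online questionnaires. The withdrawal-reasons row carries no rate.

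3. **Eight and ten sessions.** A reader might infer two conflicting programmes. The eight largely fits the Phase 2 video sessions within the 8 + 2 structure. What remains is that the wording differs between sections and the uptake row does not say which sessions it counts.

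4. **Video-sharing and privacy.** A reader might infer that this research question is not assessed at all. That is too strong: the satisfaction and experience rows and the qualitative feedback partly cover acceptability, and the ad hoc questionnaire is not shown, so it may already ask about privacy. These sources record opinion. Whether the procedures are implementable, meaning whether videos are in fact recorded and shared, has no criterion.

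**Conclusion.** The concern holds in a limited form. Uptake as defined is nearly blind to mothers who consent and never start, and is ambiguous for sessions after withdrawal, although the denominators are said to be predefined. In the main illustration this moves a primary progression criterion from amber (73.1%) to green (88.0%) while both retention rows stay green. The losses needed are not extreme: 4 of 48 at 80% attendance among starters, 9 at 90%, 13 at 100%, although in the last case follow-up retention would be amber if those mothers also missed follow-up.

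The result rests on reading the schedule as made with the first-appointment arrangements, and on assumed numbers of never-starters and assumed attendance, none of which the protocol gives. It does not show that the progression decision as a whole would be wrong, because the criteria are weighed together and larger losses would usually appear under retention.

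Separately, Table 1 cannot answer the implementability half of the video-sharing question, and the protocol's statement that privacy issues are monitored through feasibility indicators has no matching row.

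**What to change.** - Reconcile the session count between Sections 2.1.6 and 2.1.7 and Dosage and Administration, and state which sessions the uptake row counts.
- Define uptake as sessions attended / (intended sessions per mother × all consented mothers), with never-starters and sessions after withdrawal counted as not attended.
- Report the proportion of consented mothers who start, and report attendance at the video sessions separately.
- Add to Table 1 the proportion of intended videos uploaded, on the same consented denominator, with bands set by the investigators before recruitment.
- Make sure the ad hoc satisfaction questionnaire covers privacy and video-sharing.

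The cost is small: a definition, one more table row and, if the questionnaire does not already cover the topic, an item in it. Uploads already go to the study's cloud storage, so counting them needs no new collection from mothers. The article describes recruitment as not yet begun. The downside is a lower reported uptake.

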#### 2.1.2. Inclusion Criteria

The inclusion criteria for the general eligibility (applies to both groups) will be: (i) mothers in the perinatal/postnatal period aged ≥ 18 years; (ii) adequate knowledge of Italian; (iii) access to a digital device and a stable internet connection sufficient for online sessions and study assessments.

For Risk Group 1 (anxiety/depression), the inclusion criterion will be the presence of clinically significant anxiety and/or depressive symptoms, as identified through screening with the Edinburgh Postnatal Depression Scale (EPDS; cut-off score > 9) and the Generalized Anxiety Disorder 7-item scale (GAD-7; cut-off score ≥ 10). Accordingly, anxiety symptoms alone will qualify mothers for inclusion when the GAD-7 score is ≥ 10, even in the absence of clinically significant depressive symptoms.

For the Risk Group 2 (preterm birth) will be: (i) having given birth to a preterm infant, defined as gestational age < 37 weeks.

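### The eligibility rate by risk group has no place for referred mothers who meet neither risk criterion, so it does not register how many referrals lack the risk condition

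*Protocol article*

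**What the plan says.** Section 1.2 of the protocol article fixes the denominators. On referral, "the number of mothers referred will represent all mothers referred to the study by participating services or who self-refer following study advertisements". On eligibility, "Eligibility rate will be calculated as the proportion of referred mothers meeting inclusion criteria". It then requires that "All feasibility indicators will be reported for the overall sample and separately for each risk group".

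Section 2.1.2 defines the groups. "For Risk Group 1 (anxiety/depression), the inclusion criterion will be the presence of clinically significant anxiety and/or depressive symptoms, as identified through screening" with the EPDS (> 9) and the GAD-7 (≥ 10), either score being sufficient. For Risk Group 2 the criterion is "having given birth to a preterm infant, defined as gestational age < 37 weeks". Criteria common to both groups are age of at least 18 years, "adequate knowledge of Italian; (iii) access to a digital device and a stable internet connection sufficient for online sessions and study assessments". Section 2.1.3 adds exclusion criteria, which the definition of the eligibility rate does not mention.

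Section 2.1.5 lists three recruitment sources: counselling and socio-health services for symptomatic mothers, neonatal units and NICUs for mothers of preterm infants, and public advertisements, which are tied to neither group. Table 1 sets bands for "Eligible among referred": green at 60% or more, amber at 40–59%, red below 40%.

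**The concern.** A rate for a subgroup needs a denominator whose members can be identified before the outcome is known. Here, meeting the risk criterion is both part of the outcome (being eligible) and the only stated way into the subgroup. A referred mother who meets neither criterion counts in the overall denominator but in neither group's. She is also the kind of ineligible referral one would most expect from services asked to spot symptomatic mothers, and from advertisements. The count of mothers referred, when split by risk group, loses the same women. The issue is mothers with neither risk; mothers with both are a separate matter.

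The first research question in Section 1.1 asks whether eligible mothers can be identified and recruited, and the Discussion promises learning about referral pathways. If the subgroup split does not respond to below-cut-off referrals, it does not help to answer that question for the route where identification is hardest.

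**Working it through.** The article gives no expected eligibility rate and no referral counts, so there is no figure of the plan to reproduce on this point. The structure can be checked algebraically and the size shown only with assumed values.

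**Structure.** For one referral route, let
- q = share of referred mothers who meet the risk criterion;
- g = share of those who also meet the remaining criteria (age, Italian, device and internet, and exclusions if counted).

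Eligibility by route = q × g. Eligibility within a group defined by the risk criterion = (q × g) / q = g. The share q cancels, so the group rate is the same whether 30% or 80% of referrals have the risk condition.

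**Range (q and g assumed).** With q from 0.30 to 0.80 and g from 0.80 to 1.00:
- by route: from 0.30 × 0.80 = 24% to 0.80 × 1.00 = 80%, spanning red to green in Table 1;
- by criterion-defined group: 80% to 100%, which would always lie in the green range.

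**Illustration (all counts assumed, no self-referrals).** Anxiety/depression route: 60 referred, 27 above a cut-off, 26 meeting everything. Preterm route: 60 referred, 59 preterm, 57 meeting everything.

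| Reporting unit | Calculation | Rate | Table 1 range |
|---|---|---|---|
| Overall | (26 + 57)/120 = 83/120 | 69% | green |
| Risk Group 1 | 26/27 | 96% | green |
| Risk Group 2 | 57/59 | 97% | green |
| Anxiety/depression route | 26/60 | 43% | amber |
| Preterm route | 57/60 | 95% | green |

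The two groups hold 27 + 59 = 86 of the 120 referred mothers. The other 120 − 86 = 34 appear in no group: 60 − 27 = 33 from the anxiety/depression route and 60 − 59 = 1 from the preterm route. No weighting of the two group rates gives the overall 69%.

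**Sensitivity of the overall rate.** With 100 referrals per route, q = 0.30 for anxiety/depression and 0.98 for preterm:
- g = 0.95: routes 28.5% (red) and 93.1%; overall (28.5 + 93.1)/200 = 60.8%, just green; both groups 95%.
- g = 0.85: routes 25.5% (red) and 83.3%; overall (25.5 + 83.3)/200 = 54.4%, amber; both groups 85%.

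So the overall rate sometimes gives warning and sometimes does not. In neither case does the group split show where the problem lies.

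**The case against.** The strongest reply is that Section 2.1.5 pairs services with Group 1 and neonatal units with Group 2, so that by risk group may simply mean by the group for which the mother was referred. On that reading the circularity disappears for service referrals. The reading is reasonable, but the article does not adopt it, it leaves self-referrals without a group, and it works only if the route is recorded before screening.

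The second reply is that other parts of the plan would expose a weak route. This stands in part. The overall rate keeps every referred mother in its denominator. Reasons for ineligibility are a separate indicator with their own row in Table 1, and service-provider feedback is interpreted alongside the numbers. But the overall rate can stay green while one route is amber or red, and the reasons row is a qualitative grading without a denominator per route.

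Third, a reader might infer that the group rate is fixed near 100%, or that the plan cannot detect a failing route at all. The documents support neither. Mothers with the risk condition can still fail on age, language or internet access, or on exclusions such as infant medical instability if these are counted, and the article gives no value for g. Nor does Table 1 say that its bands apply to each group, so it cannot be claimed that both groups would be scored green in a progression decision.

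Finally, the article could leave the design of a referral log to the full protocol. That is fair for the log itself, but the article states both the denominators and the split by group, and those two statements do not fit together.

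**Conclusion.** The concern holds in a limited form. As Sections 1.2 and 2.1.2 stand, referred mothers meeting neither risk criterion have no group denominator, and the group-level eligibility rate is unaffected by how many such mothers are referred. The consequence is mainly for the anxiety/depression route, where membership is known only after screening, and for self-referrals. For the preterm route it should be small, because preterm status is normally known when the mother is referred.

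The size cannot be fixed from the documents. In the illustration the gap for the anxiety/depression stream is 96% against 43%, beside an overall 69%; this rests on assumed counts, equal route sizes and no self-referrals. The algebraic result, that q cancels, needs none of these assumptions, only that group membership is decided by the risk criterion. The overall rate and the ineligibility reasons remain as partial safeguards, so this is a correction worth making rather than a flaw that undermines the primary outcome.

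**What to change.** In Section 1.2, state that the referral stream is recorded at first contact, before screening: socio-health service, neonatal unit/NICU, or self-referral. Report the number referred and the proportion eligible overall and by that stream, counting a mother as eligible if she qualifies for either risk group. Use risk group as the reporting unit only from eligibility onward: consent, uptake, retention and assessment completion. Say in the same place whether exclusion criteria count in the eligibility rate. Applying the Table 1 bands to each stream is optional.

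The cost is one field in the referral log and a few words in Section 1.2, and the subgroup eligibility figures will be less favourable. Section 2.1.5 says that recruitment has not begun; the field is best added before the first referral, since the stream may be hard to reconstruct afterwards.
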